#### Arm B

In the Control group (without SBRT), palliative radiotherapy on bone metastases is allowed if necessary (pain, fracture, spinal cord compression …).

The acceptable regimens for patients in Arm1 are as follows as per consensus guidelines [18]:
30 Gy / 10 fractions / 5 fractions per week24 Gy / 6 fractions / 5 fractions per week20 Gy / 5 fractions / 5 fractions per week8 Gy / 1 fraction

The organs at risk are not delineated in the control group except for the spinal cord (Table 2).

### Ethical consideration and study registration

This Study has been approved by Nord-Ouest I Ethics Committee and French Regulatory authorities (ANSM). French ethics committee (CPP Nord-Ouest I) has approved this protocol on October 13th 2016 (reference number: CPP 02/016/2016). The study will be performed in accordance with the Declaration of Helsinki and will comply to the International Conference on Harmonization and Good Clinical Practice and General Data Protection Regulation (GDPR). This study funded by grants from French Cancer Institute (Institut National du Cancer, [name]) though PHRC program (grant number: PHRC-K 2015–149) that has no role in the collection, analysis, interpretation of results or writing of manuscripts. The study has been registered at clinicaltrials.gov (ClinicalTrials.gov NCT03143322 Registered on May 8th 2017).

Patient information and informed consent from the patient must be handled in accordance with the French regulation. Prior to the participation of a patient in the trial, this patient will be informed both verbally and in writing about the objectives of the trial, its methods, anticipated benefits and potential risks and the discomfort to which they may be exposed. The informed consent form for study and ancillaries studies, must be personally dated and signed by the patient and investigator.

### Quality Assurance of Radiation Therapy

In order to ensure patient safety and effective treatment delivery, a quality assurance protocol is implemented. Prior to opening the study, each participant centre will have to validate a dummy run by delineate targets and OARs and produce a treatment plan from a benchmark case on Aquilab software. The Quality Assurance committee will evaluate the dummy run. Patient inclusions by a centre will be allowed only after full validation. Afterwards, each participating centre will have to send planning and contouring information for the first included patient for review before the start of the radiotherapy. The QA committee according to the protocol recommendations in terms of delineation, dose constraints and treatment workflow will evaluate this treatment plan. At the end of treatment, each participating centre will have to send final review of the RT data for all included patients in SBRT arm for review. The QA committee, according to the protocol recommendations in terms of delineation, dose constraints and treatment workflow will evaluate the treatment plan for Quality Assurance.

### Systemic treatment

The patients will receive systemic standard of care for the metastases according to current oncological national recommendations and international guidelines.

### Follow-up

Patients will be seen at 3 months, 6 months post randomization and then every year for 3 years.

(Table 1). At each visit, the oncologist will conduct a history and physical examination, and assess CTC-AE toxicities, pain and quality of life. CT head, chest, abdomen and pelvis will be repeated at 6 months, then every year for 3 years. PET-CT and SPECT-CT will be repeated at 1 year. Additional Imaging should be carried out at the discretion of the physician. Additional treatment (e.g. further chemotherapy) is at the discretion of the oncologists.

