### Measurement of response

Progression-free survival will be measured as time to either progression or death, whichever occurs first. Efficacy Evaluation will be performed at baseline, at 6 months, at 1 year, then subsequently every year until the end of study, using the same imaging method as for baseline (CT scan or MRI or PET if indicated).

Lesion response will be evaluated in this study using the RECIST criteria, PERCIST Criteria and MD Anderson Criteria [19].

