### Statistical analysis

Sample size calculation: 196 patients will be randomized between 2 arms (in a 1:1 ratio). The primary endpoint is the 1-year Progression Free Survival (PFS). In the standard arm, the expected progression-free survival at 1 year is 30% (10% for lung cancer, 50% for breast cancer and 30% for prostatic cancers). In the experimental arm, we anticipate a 20% absolute increase (i.e. 30, 70 and 50%, respectively). According to Freedman’s method, accepting a two-tailed type I error of 5% and an 80% power (type II error of 20%), 178 patients (2 X 89) need to be recruited and 106 events need to be observed for the primary analysis. Assuming a 10% withdrawal rate, a total of 196 patients will need to be included.

Data analysis: All patients will be randomized after completion of the primary tumor treatment for synchronous or metachronous metastasis. The randomization will be stratified by date of metastasis (synchronous vs. metachronous) and primary tumor site (breast vs. non-small cell lung vs. prostate cancer). Statistical analysis will be performed on all the randomized patients, accordingly to the intent to treat (ITT) arm, whatever the actually received treatment. Patients without progression and alive at the time of analysis will be censored at the time of the latest assessment.

Primary Endpoint Analysis: Progression Free Survival PFS is defined as the time from randomization until the date of the first objective progression accordingly to RECIST or death (whatever its cause in the absence of progression). Patients without progression and alive at the time of analysis will be censored at the time of the latest assessment. The primary analysis will take place when 106 events have been observed. This analysis will use the logrank test, stratified on the primary location and the time of onset of the bone metastases (synchronous vs metachronous). Cox regression model will also be used to perform a sensitivity analysis taking into account the usual prognostic factors. The hazard ratio will be given with its 95% confidence interval. A *p* value <= 0.05 will be considered as statistically significant. A secondary analysis will also be performed, using the Fine and Gray model in order to take into account the competing risks (relapse in the bone, relapse in another site, death), and so to analyse the impact of the different PFS events on the trial results.

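### Progression is dated from sparse scheduled scans plus discretionary imaging in an open-label trial, so unequal imaging between arms biases the log-rank; separately, the 1-year PFS reading falls on a scan date.

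*Protocol article*

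**What the plan says.** All references are to the protocol article.

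- **Design.** The Abstract and Methods/design describe an open-label trial. Under Statistical analysis, "196 patients will be randomized between 2 arms (in a 1:1 ratio").
- **Imaging.** Follow-up and Table 1 schedule CT at month 6 and years 1, 2 and 3; the month-3 visit has no imaging. For the skeleton, "PET-CT and SPECT-CT will be repeated at 1 year", and Table 1 lists spinal MRI at month 6 and year 1 only. Between these times, "Additional Imaging should be carried out at the discretion of the physician".
- **Method of evaluation.** Measurement of response has efficacy evaluated at 6 months, 1 year and yearly after that, "using the same imaging method as for baseline (CT scan or MRI or PET if indicated").
- **Endpoint and test.** The primary endpoint is named as PFS at 1 year. PFS ends on the date progression is first objectively documented, or at death. The primary test is a stratified log-rank over all follow-up, and "106 events need to be observed for the primary analysis". Patients without an event are censored at their last assessment.

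**The concern.** Progression is not observed when it happens but when someone scans. The gaps between scheduled scans are 6 to 12 months, while the assumed control PFS of 30% at 1 year implies a median of about 7 months. Within a gap, the event date depends on whether a physician who knows the arm orders a scan. If that happens more often in one arm, its events carry earlier dates even when true progression times are identical, and the log-rank reads this as a treatment difference. RECIST standardises what counts as progression, not when anyone looks. The planned Cox and Fine and Gray analyses use the same dates.

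A second, separate effect concerns the 1-year figure. Month 12 is itself a scan time. A progression first seen at that scan counts before or after the landmark according to the appointment date.

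**Working it through.** **1. The plan's own figures.** Inputs from Statistical analysis: 1-year PFS 30% in controls; "In the experimental arm, we anticipate a 20% absolute increase", hence 50%; "accepting a two-tailed type I error of 5% and an 80% power".
- Under exponential PFS, HR = ln(0.5)/ln(0.3) = 0.576.
- Freedman: (1.960 + 0.842)² × [(1 + 0.576)/(1 − 0.576)]² ≈ 108.3 events, against 106 stated.
- Patients: 108.3/0.60 ≈ 181, against 178; 178 × 1.10 ≈ 196.

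The stated figures are reproduced within 3% and are not in dispute.

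**2. Gap length against event rate.** Control median = 12 × ln 2/(−ln 0.3) ≈ 6.9 months. Much of the control arm progresses inside the first two scan gaps.

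**3. Effect on the log-rank.** Simulation settings taken from the article: 196 patients, accrual over 48 months, analysis at the 106th event, censoring at last assessment, scans at months 6, 12, 24 and 36. Assumed: exponential PFS, uniform accrual, scan scatter with SD about half a month, and the share of progressions found early by discretionary scans, at onset or about one month later. Deaths were not modelled separately; there was no withdrawal and the test was unstratified. At 1,000 runs per case, the Monte Carlo standard error near 5% is √(0.05 × 0.95/1000) ≈ 0.7 points.

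No true effect, actual-date log-rank:

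| Early detection, control/SBRT | False result (nominal 2.5% per direction) |
|---|---|
| 20%/10% | about 3-5% favouring SBRT |
| 30%/10% | about 4-8% favouring SBRT |
| 40%/10% | about 9-10% favouring SBRT |
| 10%/30% | about 6-8% favouring control |

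In the design case (50% against 30%), 10/30% lowers power from about 74% to 63%. With equal detection in both arms, the error stays near nominal.

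**4. Effect on the 1-year reading.** True PFS at month 6 is √0.30 = 54.8% in controls and √0.50 = 70.7% with SBRT. With no detection between scans, the curve stays at that level until the 12-month scan. If half the 12-month scans fall after month 12, the reading is roughly midway: (54.8 + 30)/2 ≈ 42% and (70.7 + 50)/2 ≈ 60%. Some early detection and the article's censoring rule bring this down to about 34-39% for a true 30% and 54-56% for a true 50%. With equal scatter (SD 14 days) and no true effect, the log-rank error was 5.5%, so this effect alone does not disturb the test.

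**5. Visit-assigned dating.** Placing progression and censoring at nominal visit times returns two-sided error to about 4-6%, gives 1-year PFS of about 29-30% and 49%, and costs essentially no power (77% against 74% with actual dates).

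**6. Reading the actual-date curve at month 13 instead.** This gives about 24% for a true 30%. Event-free patients not yet scanned again are censored at their 12-month scan and leave the risk set, so progressions at slightly later 12-month scans are divided by too small a number.

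**The case against.** **The detection shares and their direction are assumed.** This stands. A reader might infer that controls will be imaged more, because the Arm B section allows palliative radiotherapy for symptoms. That section says nothing about imaging, and Table 1 applies to both arms. The bias could run either way.

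**The sizes can be overstated.** A reader might let follow-up run to a fixed month 60 and obtain about 15% at 30/10% and 25% at 40/10%. The article fixes the analysis at 106 events, and under that rule the figures are smaller. Deaths, which are dated exactly, would dilute the bias further.

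**The primary test is not a 12-month comparison.** This also stands. A reader might infer that a few days' scan delay could create a positive trial. A delay common to both arms leaves the log-rank nearly unchanged; only a delay differing by arm would bias it. Nothing in the article suggests one, and visits in both arms are timed from randomisation.

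**The planning 30% may already be PFS as measured by scans.** The article does not say. The overstatement in the 1-year reading is relative to true time of progression.

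**Imaging methods.** A reader might infer that 2- and 3-year PFS rest on a wholly different method from 1-year PFS. They do not: CT is scheduled at every efficacy visit, and Measurement of response qualifies PET as used where indicated. What drops out after year 1 is scheduled PET/SPECT-CT and spinal MRI.

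**Scan windows, blinded review and dating rules may be in the full protocol or analysis plan.** Their absence here is not counted. The point rests on what the article does fix: sparse scans, discretionary imaging, open label, event-date log-rank and censoring at last assessment.

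**Conclusion.** The concern holds in a limited form. Followed as written, the plan lets unequal discretionary imaging bias the primary log-rank and hazard ratio in favour of the less-imaged arm. For moderate imbalances the one-directional false-positive rate rises from 2.5% to somewhere between 3% and 10%. If the SBRT arm is imaged more, the cost is power instead, about 11 points at 10/30%. These sizes depend on assumed detection shares, exponential PFS and no separately modelled deaths; the article does not show that any imbalance will occur.

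The 1-year estimate is a separate matter. Read at exactly 12 months, it is too high by roughly 4 to 9 points when scans scatter around that date, to a similar degree in both arms and without consequence for the log-rank. The imaging-method inconsistency is minor.

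**What to change.** - Pre-specify an analysis, as primary or as a named sensitivity analysis beside the actual-date log-rank, that assigns progression found at an unscheduled scan to the next scheduled assessment. Place both progression and censoring at nominal visit times and keep deaths at their actual dates. An interval-censored equivalent would serve.
- Report 1-year PFS from that analysis, not from Kaplan-Meier at day 365 and not from the actual-date curve at month 13.
- Report the number and timing of scans by arm, so that any imbalance is visible.
- Reconcile Measurement of response with Table 1. State that PET/SPECT-CT and spinal MRI are not scheduled after year 1, so 2- and 3-year PFS rest on scheduled CT.

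The cost is wording and slightly coarser event dates. No extra scans or patients are needed, and physicians' freedom to order imaging is unaffected.

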### Measurement of response

Progression-free survival will be measured as time to either progression or death, whichever occurs first. Efficacy Evaluation will be performed at baseline, at 6 months, at 1 year, then subsequently every year until the end of study, using the same imaging method as for baseline (CT scan or MRI or PET if indicated).

Lesion response will be evaluated in this study using the RECIST criteria, PERCIST Criteria and MD Anderson Criteria [19].

### Statistical analysis

Sample size calculation: 196 patients will be randomized between 2 arms (in a 1:1 ratio). The primary endpoint is the 1-year Progression Free Survival (PFS). In the standard arm, the expected progression-free survival at 1 year is 30% (10% for lung cancer, 50% for breast cancer and 30% for prostatic cancers). In the experimental arm, we anticipate a 20% absolute increase (i.e. 30, 70 and 50%, respectively). According to Freedman’s method, accepting a two-tailed type I error of 5% and an 80% power (type II error of 20%), 178 patients (2 X 89) need to be recruited and 106 events need to be observed for the primary analysis. Assuming a 10% withdrawal rate, a total of 196 patients will need to be included.

Data analysis: All patients will be randomized after completion of the primary tumor treatment for synchronous or metachronous metastasis. The randomization will be stratified by date of metastasis (synchronous vs. metachronous) and primary tumor site (breast vs. non-small cell lung vs. prostate cancer). Statistical analysis will be performed on all the randomized patients, accordingly to the intent to treat (ITT) arm, whatever the actually received treatment. Patients without progression and alive at the time of analysis will be censored at the time of the latest assessment.

Primary Endpoint Analysis: Progression Free Survival PFS is defined as the time from randomization until the date of the first objective progression accordingly to RECIST or death (whatever its cause in the absence of progression). Patients without progression and alive at the time of analysis will be censored at the time of the latest assessment. The primary analysis will take place when 106 events have been observed. This analysis will use the logrank test, stratified on the primary location and the time of onset of the bone metastases (synchronous vs metachronous). Cox regression model will also be used to perform a sensitivity analysis taking into account the usual prognostic factors. The hazard ratio will be given with its 95% confidence interval. A *p* value <= 0.05 will be considered as statistically significant. A secondary analysis will also be performed, using the Fine and Gray model in order to take into account the competing risks (relapse in the bone, relapse in another site, death), and so to analyse the impact of the different PFS events on the trial results.

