#### Secondary endpoints

*The secondary endpoints are as follow:*
PFS at 2 and 3 years defined as the time from randomization until the date of the first objective progression or deathBone progression free-survival (BPFS) at 1 year defined as the time from the date of randomization to the date of documented bone progression at the level at the entire skeleton.Local control (LC) at 1 year defined as the time from the date of randomization to the date of a documented local event at the level of bone oligometastases presents at randomization.Cancer-specific survival (CSS) at 1, 2 and 3 years defined as the time from the date of randomization to the date of documented death from cancer or complication from the treatment.Overall survival (OS) at 1, 2 and 3 years defined as the time from the date of randomization to the date of documented death from any cause.Acute and late Toxicity at 1, 2 and 3 years assessed by the National Cancer Institute Common Toxicity Criteria (NCI CTC) version 4.0.Quality of Life assessed using self-administered questionnaires (EORTC-QLQ-C30, EORTC-QLQ-BM22, and EQ-5D-3L) [12–14].Pain score evaluated accordingly to Numeric Scale.The Cost- Utility /Cost-Effectiveness / Budget Impact analysis performed on QALYs (Quality-Adjusted Life Years) and ICERs (Incremental Cost-Effectiveness Ratios) calculation based on EQ-5D-3L questionnaire.

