### Data safety monitoring committee

An Data Safety Monitoring Committee (DSMC), with expertise and experience in the pathology, and without direct involvement in the conduct of the trial, will be set up specifically to guarantee effective protection of patients, insure the ethical conduct of the trial, benefit/risk ratio of the trial, and to ensure the independent review of the scientific results during the trial and at the end of the trial. The DSMC will meet after 60 patients are accrued in the experimental arm to review toxicity outcomes and compliance.

The DSMC may recommend the early termination of the trial if one of the following conditions is met: an unacceptable toxicity or all available data from the trial or any other source of information are sufficiently convincing to influence the therapeutical practices of the majority of clinicians. The DSMC has only a consultative role; it will inform the sponsor who will decide whether the DSMC recommendation will be followed. An adverse event (AE) is defined as any untoward medical occurrence, in a patient or clinical trial subject treated by a medicinal product and which does not necessarily have a causal relationship with this treatment. The assessment of whether there is a reasonable causal relationship is made by the investigator. Notification must be carried out immediately by fax to the R&D UNICANCER pharmacovigilance unit by sending the form “notification of a Serious Adverse Effects”, located in the Investigator Master File, completed as precisely as possible, dated and signed by the physician-investigator.

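### Read literally, the intention-to-treat rule also covers toxicity, so Arm A patients who never start SBRT would modestly dilute the reported SBRT toxicity rate

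*Protocol article*

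**What the plan says.** The protocol article, Statistical analysis, has a paragraph headed Data analysis that stands before the separate paragraph on the primary endpoint. It states: "Statistical analysis will be performed on all the randomized patients, accordingly to the intent to treat (ITT) arm, whatever the actually received treatment". The sentence names no endpoint, and the article defines no other analysis population.

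Toxicity is listed under Secondary endpoints: "Acute and late Toxicity at 1, 2 and 3 years assessed by the National Cancer Institute Common Toxicity Criteria (NCI CTC) version 4.0". The article describes no analysis method for it.

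Three other places bear on the point:

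- Data safety monitoring committee: "The DSMC will meet after 60 patients are accrued in the experimental arm to review toxicity outcomes and compliance". The trigger counts patients entered into Arm A, not patients treated with SBRT.
- Statistical analysis, sample size: "Assuming a 10% withdrawal rate, a total of 196 patients will need to be included". This is the only attrition figure in the article.
- Arm B: "In the Control group (without SBRT), palliative radiotherapy on bone metastases is allowed if necessary". The control strategy includes palliative radiotherapy; SBRT is not part of it.

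**The concern.** Analysis by allocated arm is the right choice for PFS. For harms, the reader also needs the rate among people who actually had the treatment. A patient allocated to SBRT who never receives a fraction cannot have SBRT toxicity, yet adds one to the denominator. If SBRT adds toxicity, every such patient lowers the reported rate and the reported excess over control.

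Some non-receipt is foreseeable. Between allocation to Arm A and the first fraction come the planning CT with immobilisation, image fusion, fiducials where needed, organ-at-risk constraints and, for the first patient at each centre, a plan review before radiotherapy starts.

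Toxicity is a main cost to weigh against a PFS gain, and it is one of the grounds on which the DSMC may recommend stopping. A rule that pulls the rate towards no harm should not apply to it by default.

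**Working it through.** **The plan's own figure.** The article gives no toxicity rate, no rate of failing to start SBRT and no rate of SBRT use in Arm B, so there is no stated toxicity figure to reproduce. The 10% allowance can be traced: 178 × 1.10 = 195.8, rounded up to 196, or 98 per arm. It inflates the PFS sample for withdrawal from the trial as a whole. It is not a forecast of patients who never start SBRT. It serves below only as a reference value, and placing all of it before the first fraction is the extreme reading of it.

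**Scope of the rule, by reading.** The sentence stands in the general paragraph, and the primary endpoint paragraph repeats the censoring rule but not the population rule. The general paragraph is therefore the only place where a population is set, and nothing exempts toxicity. Against this, the sentence is followed at once by a PFS censoring rule, and every method in the section (logrank, Cox, Fine and Gray) concerns PFS. Coverage of toxicity is the literal reading, not an express statement.

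**Size of the dilution.** Let r be the toxicity rate in Arm A patients who receive SBRT, b the rate without SBRT, and f the share of Arm A who never start. Assume that non-starters have rate b and that no one in Arm B receives SBRT.

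- Rate reported for Arm A = (1 − f) × r + f × b
- Reported excess = (1 − f) × (r − b)

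With assumed values r = 20% and b = 5%, the true excess is 15 points:

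| Non-receipt f (assumed) | Arm A rate reported | Excess reported |
|---|---|---|
| 2% | 19.70% | 14.70 points |
| 5% | 19.25% | 14.25 points |
| 10% | 18.50% | 13.50 points |
| 20% | 17.00% | 12.00 points |

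For 5% to 10% non-receipt the excess of 15 points is thus reported as 14.3 to 13.5.

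**Compared with sampling error.** With 98 per arm and rates of 20% and 5%, the standard error of the difference is √[(0.20 × 0.80 + 0.05 × 0.95) / 98] = √(0.2075 / 98) = 0.046, or 4.6 points. The 95% interval is about ±9 points. A bias of 1.5 points is about one third of a standard error.

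**At the DSMC review.** If 10% of the 60 accrued patients had not been treated (an assumption), 54 would have been exposed. For a type of event not yet seen, the rule-of-three upper bound is 3/60 = 5.0% on patients accrued and 3/54 = 5.6% on patients treated.

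**The case against.** The strongest objection is that the article never says toxicity is analysed by intention to treat. The sentence fits an efficacy rule, and a safety population is commonly left to the full protocol or the SAP, neither of which is shown. Part of this stands: the absence of a safety set from a journal article is not a finding. What remains is a published rule worded without limit. A later document that used a different population for toxicity would depart from that wording, so the sentence needs limiting even if only efficacy was meant.

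A reader might go further and infer that SBRT given in Arm B would be charged to the control and so widen the bias. The documents do not support this. The control group is described as being without SBRT and no crossover is planned. The Follow-up section says "Additional treatment (e.g. further chemotherapy) is at the discretion of the oncologists", which neither names nor excludes SBRT. Any crossover rate would be invented.

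A reader might also infer that toxicity from palliative bone radiotherapy is wrongly counted in Arm B. It is not. That treatment is allowed there, belongs to the control strategy, and its toxicity rightly counts in that arm.

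Two further objections stand in part. A by-arm toxicity comparison is a legitimate randomised comparison of strategies, so it should be kept. And an as-treated comparison has biases of its own: if Arm A non-starters, who may be deteriorating, were moved into the comparator, they could raise its event rate and mask harm. They should therefore be listed separately and not pooled with Arm B.

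Finally, the DSMC reviews compliance together with toxicity, and the quality assurance section requires final radiotherapy data for all included patients in the SBRT arm. Exposure should therefore be known. This lessens the risk of an unnoticed dilution, but it does not set the denominator.

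**Conclusion.** The point holds as a minor, inexpensive improvement. On its plain wording the population rule keeps Arm A patients who never start SBRT in the SBRT toxicity denominator, and the bias runs towards no harm.

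Its size is small: about 0.75 to 1.5 points on an assumed excess of 15 points at 5% to 10% non-receipt, well inside the sampling error. The excess and the non-receipt rates are assumptions, as is the premise that non-starters have the background toxicity rate. If few patients fail to start, the effect is negligible.

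Neither the PFS analysis nor the event count or sample size is affected. The documents do not support a wider claim that every analysis is expressly by allocation, or that control toxicity is inflated.

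**What to change.** 1. Limit the intention-to-treat sentence to the efficacy endpoints.
2. State that SBRT toxicity is reported among Arm A patients who received at least one SBRT fraction, compared with Arm B patients who received no SBRT. Palliative radiotherapy in Arm B stays part of the control strategy.
3. List separately the Arm A patients who never started SBRT and any Arm B patient who was given SBRT.
4. Keep the toxicity table by randomised arm alongside, as the strictly randomised comparison.
5. For the DSMC review, show the number treated with SBRT next to the number accrued, and give the toxicity rate on the number treated.

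The cost is one sentence and one extra table set. The as-treated groups are not strictly randomised, so differences between them may partly reflect who started treatment. The by-arm table lets the reader judge this.
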